### Intervention

In the intervention group, CRP POCT can be used on-site for residents with suspected LRTI in addition to usual care. The control group provides usual care without the possibility for CRP POCT. Usual care may in some cases include CRP-measurement via laboratory assessment, or, in rare cases, sputum culture or chest radiography.

CRP-measurement via laboratory assessment differs from CRP POCT with regard to the type of blood collection (venipuncture respectively finger prick), location (the blood is taken to an external lab respectively the measurement is performed on-site), time-to-results (hours-days versus minutes), and potential frequency of measurements (once-twice a week on average versus 24/7).

During the trial, physicians in the intervention group decide on whether or not to use CRP POCT and, if performed, they consider the results alongside clinical features of the patient in their prescribing decision.

Prior to study commencement, the intervention group will receive two training sessions: 1) a medical training session and 2) a technical POCT training session.

#### Medical training session

Members of the research team will provide a medical training for medical doctors and nurse practitioners in the intervention group on the use and interpretation of CRP POCT for the diagnosis of LRTI. The contents of the training are based on the LRTI guideline for the NH setting (of the Dutch Association of Elderly Care Physicians and Social Geriatricians), and on extensive literature research. Topics include characteristics of the CRP POCT instrument (e.g. validity, reliability, and limitations), evidence and lessons learnt from the use of CRP POCT in general practice, and instructions specific to the NH setting. Specific instructions include the use of cut-off-values for antibiotic prescribing that are included in the LRTI guideline, i.e. a lower limit of 20 mg/L and an upper limit of 60 mg/L. The latter is different from the cut-off-value in the general practice population (i.e. 100 mg/L), and was based on a NH study that showed adequate discriminatory power for distinguishing pneumonia with this CRP-value [33].

#### Technical POCT training session

The POCT expert team from a non-commercial, EU accredited laboratory (Saltro diagnostic center, Utrecht) will provide the technical instructions to the intervention group of medical doctors and nurses who will perform CRP POCT during the trial. In each NH organization, a ‘trainer’ is appointed, who will train new employees during the study period. The technical training takes place after the medical training, within a period of 2 months. After the technical training until study commencement, the intervention group will have a run-in period to get used to CRP POCT in routine practice, varying from 1 week to 3 months per organization. The POCT expert team provides technical assistance during the trial and monitors quality throughout the study period.

#### Technical features of CRP POCT

The CRP POCT instrument that is used in this study (QuikRead go®, Orion Diagnostica Oy) has been shown to have adequate analytical accuracy and agreement with laboratory measurements [43, 44]. The analyzer has a built-in self-check procedure that secures its correct use and correct results. In case of errors, the display will show a specific error notification.

The test principle relies on immunoturbidic measurement of turbidity changes in the sample due to the reaction of CRP with the reagent, i.e. monoclonal antihuman CRP F (ab) 2 fragments-coated microparticles.

The blood sample obtained by finger-prick, using a 20 μl capillary tube, is dispensed into the cuvette, which hemolyzes the blood cells in the sample. Next, the cuvette is placed into the analyzer, which measures the hematocrit level before adding the reagent from the cap into the cuvette. With the reagent added, the microparticles bind to the CRP in the sample. The turbidity of the sample is then calculated using calibration information and with correction for the hematocrit level. In total, the CRP POCT measurement takes 2 to 4 min.

### Data collection

The period of data collection for each participant is 3 weeks. In this period, three case report forms (CRFs) are to be completed by the physician: at index consultation (T0), and at one (T1) and three (T2) weeks after index consultation. The CRFs are integrated into the electronic patient record system: eligibility criteria appear in an eligibility form if physicians diagnose a suspected LRTI. If eligible, CRFs are available electronically to be completed at due time points.

The T0 CRF contains questions on patient characteristics (principal diagnosis at NH admission, comorbid conditions, use of immunosuppressive medication, and recent surgery), signs and symptoms, performed diagnostics (CRP POCT and/or other), and antibiotic prescribing (yes/no, type). The T1 and T2 CRF include follow-up on patient recovery, changes in policy (additional diagnostics performed, hospital referral, and treatment changes). In addition, pharmacy data will be collected on total antibiotic prescribing in the NH during the study period. Figure 1 depicts the timeline of patient enrollment, intervention, and data collection.

**Fig. 1 Fig1:**
[figure not shown]
schedule of patient enrollment, intervention, and data collection

### Informed consent procedure

The informed consent procedure consists of two steps:
Written information is provided to either the patient or representative (depending on competence status, as judged by the physician), prior to study commencement or upon NH admission. At this time and throughout the study period, the patient/representative is given the opportunity to opt-out. Opting-out is registered within the electronic patient record, which deactivates potential eligibility notifications*.* If opted-out, step two will not be initiated.In case of a suspected LRTI, the physician contacts the patient/representative to ask for consent, which includes the opportunity to ask questions. In both groups, consent is asked for data collection. In the intervention group, consent is additionally asked for performing CRP POCT. An exceptional case is the situation in which the patient or the representative is not able to provide consent at the time of the diagnosis (e.g. if the patient is too ill or if the representative is not present): in that case, a physician can use CRP POCT as part of usual care if this is considered to support proper management. Consent is asked in retrospect (i.e. deferred consent), as soon as possible and at an appropriate moment, for data collection and potential future CRP POCT use. After the physician confirms within the CRF that the informed consent form is signed, data from the CRF are automatically sent to the research team in pseudonymized form via a secure web-portal.

### Outcomes

The primary study outcome is antibiotic prescribing for suspected LRTI at index consultation (yes/no). Secondary study outcomes include physician-reported recovery at one and 3 weeks after index consultation, use of additional diagnostics within 3 weeks after the index consultation (including repeated CRP measures), changes in treatment policy within 3 weeks after the index consultation, hospitalization, complications, (all-cause) mortality, and total antibiotic prescribing on the NH level.

Costs that will be included in the economic evaluation (health care perspective) are related to the use of CRP POCT, prescription of antibiotics, consultation by physicians in the NH, additional diagnostic tests, hospital admissions and other health care utilization for LRTI and complications of LRTI treatment. Costs will be measured from the CRFs and valued using the guidelines of the National Health Care Institute [45].

### Data analysis

The primary analysis will be intention-to-treat and will assess the effect of CRP POCT on antibiotic prescribing for suspected LRTI at index consultation. A three-level logistic regression model will be used to account for variation at the NH/physician/patient level. If there is no indication of random effects at the physician level, the model will be reduced to a two-level model. Multilevel regression modeling will similarly be used to compare secondary study outcomes between the two groups (linear or logistic, as appropriate). A second-order penalized quasi-likelihood estimation procedure will be applied.

Pharmacy data on total antibiotic prescribing will be explored descriptively, in order to describe the potential impact of adjusted antibiotic prescribing for LRTI on total antibiotic prescribing within intervention NHs, compared to control NHs. Total antibiotic prescriptions will be expressed per 1000 residents per year.

Data of patients in the intervention group will be used to explore potential relations between CRP POCT values and; 1) signs/symptoms in NH patients with suspected LRTI, and 2) antibiotic treatment. Multiple linear or logistic (as appropriate) regression modeling will be performed.

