## Background

Lower respiratory tract infections (LRTI) such as pneumonia are common in nursing homes (NHs) [1]. In Dutch NHs in 2015, the incidence of suspected pneumonia was approximately 200 cases per 1000 residents, with a typical pattern of seasonal variation (i.e. winter peak, summer trough) [2]. NH residents are at increased risk of respiratory infections due to factors typical for this population, such as frailty and comorbidities. Also, the crowded nature of NH residence and frequent nursing staff-resident contact may facilitate the transmission of pathogens [1, 3–5]. The incidence of nursing home-acquired pneumonia (NHAP) can be up to tenfold of the incidence in elderly living in the community [1, 6–10]. Moreover, the severity and prognosis of NHAP is worse compared to pneumonia among elderly living in the community [11–13]. NH LRTI episodes may range from self-limiting viral infections, to severe NHAP requiring hospitalization or causing rapid death [3, 14–16].

An early diagnosis of NHAP enables prompt and appropriate management, decreases the risk of complications and mortality, and reduces overall health care costs [16–18]. Yet, physicians often find it difficult to estimate the severity and potential outcome of the LRTI episode [19, 20]. Moreover, NH residents often have atypical clinical presentation, multi-morbidity, and a diminished ability to recall or describe symptoms (e.g. due to cognitive impairment). Diagnostic tools are often not available (e.g. chest X-ray) or applicable (e.g. sputum culture) in this setting [3, 5, 17, 21, 22]. Overall, diagnostic uncertainty often results in (empirical) antibiotic prescribing to be ‘better safe than sorry’. This attitude towards antibiotic prescribing may be reinforced by external factors, such as (perceived) expectations of patients or family members towards antibiotic prescribing [23, 24].

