### Sample size calculation

Based on previous study data [40], we expect 15% less antibiotic prescriptions in the intervention group compared to the control group (i.e. 80% respectively 95%). In order to detect this difference, with 80% power and at a 5% significance level, 146 cases would be required. If we randomize eleven NH organizations with an average number of 400 residents (cluster size) and with an intracluster correlation coefficient of 0.06, the required number of cases is 671 [42].

The expected incidence rate of suspected LRTI is 3.5 cases per 1.000 resident-care weeks in NHs [2]. Based on previous study data, we expect that at most 10% of cases will not meet inclusion criteria and that 75% of eligible cases provide informed consent for study participation. This means that of all LRTI cases, approximately 70% can be included in the study, which translates into an expected 2.4 suspected LRTI per 1.000 resident-care weeks.

ln order to include 671 cases of LRTI in eleven organizations with an average number of 400 residents the study period totals to 1.5 year, with a small margin for potential suboptimal inclusion.

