#### Control group

During the study we remain vigilant towards potential post-randomization recruitment bias: the control group might gradually or throughout the trial be less inclined to recruit patients, given the absence of the intervention [14, 20]. We anticipate the need for incentives especially in the control group during the trial. Another phenomenon that may arise in the control group is the Hawthorne effect, that is, a shift towards more rational antibiotic prescribing because of the physician’s awareness of being observed [29, 47].

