### Reflection on study context

#### Antibiotic stewardship in NHs

In the Netherlands in recent years, antimicrobial resistance in different settings such as NHs has gained a more prominent place on the research and public health agenda. Antibiotic stewardship efforts are widely supported and developed for the NH setting by different parties. During the UPCARE study, it is important to monitor such activities as they might influence the primary outcome.

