#### LRTI guideline for the NH setting

Around the start of data collection, a LRTI guideline was published for the NH setting by the Dutch Association of Elderly Care Physicians and Social Geriatricians. In this guideline, physicians are instructed to assess the CRP-level for patients who are moderately ill and who have certain clinical signs and symptoms that do not indicate LRTI unambiguously. In the guideline, CRP POCT is not specifically advised for CRP-measurement, as evidence for its (cost-) effectiveness is currently insufficient. With the UPCARE study we aim to address this knowledge gap.

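### If control recruitment tails off while prescribing drifts, the pooled primary comparison, which states no calendar-time term, leans modestly toward CRP POCT; prespecify one

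*Protocol article*

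**What the plan says.** Data analysis (protocol article) sets an intention-to-treat comparison of antibiotic prescribing at the index consultation: "A three-level logistic regression model will be used to account for variation at the NH/physician/patient level". It adds a rule for dropping the physician level and names the estimation procedure. It lists no fixed effects, so calendar time, season and baseline covariates all go unmentioned. The section on cost-effectiveness and cost-benefit analyses, by contrast, does say that baseline characteristics will be corrected for.

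Three parts of the Discussion bear on time:

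- Control group: "the control group might gradually or throughout the trial be less inclined to recruit patients, given the absence of the intervention". The response given is vigilance and incentives, mainly for controls.
- Antibiotic stewardship in NHs: "During the UPCARE study, it is important to monitor such activities as they might influence the primary outcome". The response given is monitoring.
- LRTI guideline for the NH setting: "Around the start of data collection, a LRTI guideline was published for the NH setting". No response in the analysis is given.

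Study design and population makes the arms parallel, with organisations randomised 1:1 and data collected from September 2018 for about 1.5 years.

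**The concern.** Each case enters only if a physician enrols it. If enrolment falls off in control homes but not in intervention homes, the control sample is weighted to the early months and the intervention sample is not. If prescribing without CRP POCT also falls over those months, through stewardship activity or gradual uptake of the guideline, the control percentage is too high for a fair comparison and CRP POCT is credited with part of the drift.

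Random effects for home and physician do not remove this, because the difference in calendar mix lies between the arms. Incentives and monitoring may make it less likely, but they do not take it out of the estimate once it has occurred. The error would favour the intervention, in a trial whose physicians know their allocation.

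**Working it through.** **Inputs from the documents.** Sample size calculation: 95% versus 80% prescribing, 5% significance, 80% power, 146 cases before clustering, intracluster correlation (ICC) 0.06, 11 organisations, 671 cases. The fall in prescribing and the decline in control recruitment are not given, so both are assumptions below.

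**The plan's own figures.**

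- n per arm = (1.96 + 0.84)² × (0.95×0.05 + 0.80×0.20) / 0.15² = 72.4, so 73 per arm and 146 in total.
- 671/11 = 61 cases per organisation; design effect = 1 + 60×0.06 = 4.6; 146 × 4.6 = 671.6.

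Both reproduce. The 4.6 is reused below.

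**Bias with gradual change.** Let time t run from 0 to 1. Prescribing falls linearly by D points in both arms, and CRP POCT has no effect. Intervention inclusions are uniform, so their mean time is 0.5. The control inclusion rate is proportional to 1 − q·t, so the mean control time is (1/2 − q/3)/(1 − q/2).

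Bias toward CRP POCT = D × (0.5 − mean control time).

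| Control decline q | Mean control time | D = 5 | D = 10 | D = 20 |
|---|---|---|---|---|
| 0% | 0.500 | 0 | 0 | 0 |
| 50% | 0.444 | 0.3 | 0.6 | 1.1 |
| 75% | 0.400 | 0.5 | 1.0 | 2.0 |
| 100% | 0.333 | 0.8 | 1.7 | 3.3 |

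Entries are percentage points. The first row shows that a common trend with parallel recruitment is harmless.

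Large-sample logistic fits without clustering agree. For D = 10 the unadjusted odds ratio is 0.94 (q = 50%) and 0.82 (q = 100%); for D = 20 it is 0.91 and 0.74. With a time term it returns to between 0.99 and 1.02.

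**Type I error at the planned design effect.** At about 90% prescribing and 335.5 cases per arm, SE = √(4.6 × 2 × 0.9 × 0.1 / 335.5) = 0.050, or 5.0 points. For bias b, the error rate is Φ(−1.96 + b/SE) + Φ(−1.96 − b/SE):

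- D = 10, q = 50% (b = 0.6): about 5.2%
- D = 10, q = 100% (b = 1.7): 6.3%
- D = 20, q = 100% (b = 3.3): about 10%

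**Cross-check in two halves.** Bias = (control share in first half − intervention share) × fall between halves. With the intervention at 50/50 and prescribing falling from 95% to 85%, control mixes of 60/40, 70/30 and 80/20 give 0.1×10 = 1, 0.2×10 = 2 and 0.3×10 = 3 points. Simulated null trials (6 versus 5 organisations, 61 cases each, cluster-level t-test, ICC about 0.06 on the proportion scale) give type I error of roughly 5%, 6% and 9 to 10%. A half-year term brings the bias to about zero. In runs with a smaller cluster variance (logit SD 0.46), the SD of the estimate was the same with and without the term: 0.033 at 70/30 and 0.031 at 80/20. The t-test stands in for the planned multilevel model.

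**The case against.** The strongest objection is that this argues from silence. Data analysis lists no fixed effects, and a condensed article commonly leaves them to a full protocol or analysis plan. That stands to this extent: one can say that no calendar-time term is stated, not that the model has none. What remains is that the article names two time-related threats to its primary comparison and answers both with operational measures only, although it does state covariate correction for the cost analysis.

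Several stronger readings are tempting and are not supported:

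- A reader might infer that the trial expects control recruitment to fall and prescribing to shift. The text says only that each might happen. Recruitment that is uniformly lower in controls throughout would not change the calendar mix.
- A reader might infer that any time trend can pass for a CRP POCT effect. With concurrent arms it cannot, unless inclusion times also differ.
- The seasonal pattern in Background ("with a typical pattern of seasonal variation (i.e. winter peak, summer trough") concerns the incidence of suspected pneumonia, not the chance of a prescription.
- The guideline appeared around the start, so it covers nearly the whole period in both arms. Only gradual uptake, which the text does not state, would make a trend.
- A Hawthorne shift in controls lowers control prescribing and so dilutes the effect. A common period term does not remove it.

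The larger scenarios are also demanding. Under linear decline, control recruitment that falls to zero gives a 75/25 split, so 80/20 needs a step change: a 75% drop in the second half. A 10-point fall between half averages is a 20-point fall over the trial if the drift is gradual.

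Finally, simulations with logit SD 0.46 give error rates of 7 to 9% at 70/30 and 13% at 80/20. That SD is ICC 0.06 on the latent scale but only about 0.01 to 0.03 on the proportion scale, where the design effect of 4.6 applies. Those rates should not be used.

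**Conclusion.** The point holds as a conditional one. If control recruitment declines and prescribing without CRP POCT falls over the same months, the pooled comparison as described is biased toward CRP POCT. Under the assumed ranges the bias is about 0.3 to 3 points against a planned 15, and it is 1.1 points or less unless control recruitment falls by more than half. At a proportion-scale ICC of about 0.06, type I error is about 5 to 6% in moderate scenarios and up to about 10% in extreme ones. If recruitment stays parallel, there is no bias.

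The direction is firm when both conditions occur; the size rests wholly on assumptions, because the documents give neither the fall nor the decline. Severity is minor to low-end should-fix. The case for acting is that the remedy is nearly free and that choosing it after seeing control recruitment fall would be post hoc.

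**What to change.** In Data analysis, prespecify calendar period of the index consultation as a fixed effect in the primary multilevel model, or at least as a prespecified sensitivity analysis. Four periods would serve, for example: September 2018 to February 2019, March to May 2019, June to August 2019, and September 2019 to the end. Report a table of inclusions by arm and period, so that a reader can see whether the calendar mix differed. Repeating the comparison in the first 12 months is optional.

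The cost is one sentence and, with four periods, three extra parameters for about 671 cases. Simulation of a single half-year term showed no loss of precision; four categories were not tested. Data collection does not list the index date, but the follow-up forms are timed from the index consultation, so the date must be known.

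The term does not correct selective enrolment by severity or a Hawthorne shift confined to controls. It also does not remove chance imbalance from stewardship activity in single organisations.

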**Methods/design:**

A cluster randomized controlled trial will be conducted in eleven nursing homes in the Netherlands, with the nursing home as the unit of randomization. Residents with suspected LRTI who reside at a psychogeriatric, somatic, or geriatric rehabilitation ward are eligible for study participation. Nursing homes in the intervention group will provide care as usual with the possibility to use CRP POCT, and the control group will provide care as usual without CRP POCT for residents with (suspected) LRTI. Data will be collected from September 2018 for approximately 1.5 year, using case report forms that are integrated in the electronic patient record system. The primary study outcome is antibiotic prescribing for suspected LRTI at index consultation (yes/no).

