## Methods/design

### Study design and population

The UPCARE study design is a cluster RCT, with randomization at NH organization level. This randomization level was chosen because of our pragmatic trial design and in order to avoid spill-over effects. Data collection starts September 2018 and will, based on calculations of expected inclusion rate, last approximately 1.5 year. Eleven NH organizations across the Netherlands will participate in the study. A simple randomization procedure using Microsoft Office Excel 2016 software will be performed by the research team to allocate participating organizations to either the control or intervention group (1:1).

Dutch NHs typically have three types of specialized wards: somatic wards that accommodate physically disabled residents, psychogeriatric wards that accommodate residents with dementia, and geriatric rehabilitation wards. NH admission to one of these wards and the required level of care is determined by a standardized assessment performed by a government agency (“Centrum Indicatiestelling Zorg” (CIZ)). Unique to Dutch NHs is the employment of specialized ‘elderly care physicians’. Other NH prescribers may include physicians with other specializations or general medical training, elderly care physicians in training, and nurse practitioners. Dutch NH medical care typically excludes the use of intravenous drugs, and hospital referrals are limited [40, 41].

The study population comprises NH residents from psychogeriatric, geriatric rehabilitation, or somatic wards, who are newly diagnosed with a ‘suspected LRTI’. Patients are excluded if they receive palliative/terminal care with a restrictive antibiotic policy, if they do not wish to be treated with antibiotics, if they are using antibiotics (currently or in the past week), or if they have an infection other than the suspected LRTI (currently or in the past week).

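### With eleven randomised organisations, the stated 5% level and 80% power are not both delivered: the sample size rests on normal quantiles and the analysis makes no few-cluster allowance

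*Protocol article*

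**What the plan says.** The protocol article, under Study design and population, describes a cluster trial "with randomization at NH organization level" with 1:1 allocation, and adds: "Eleven NH organizations across the Netherlands will participate in the study". The abstract describes the same design "with the nursing home as the unit of randomization".

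Under Sample size calculation, the expected prescribing rates are 95% in the control group and 80% in the intervention group. Before clustering, "with 80% power and at a 5% significance level, 146 cases would be required". With eleven organisations and an intracluster correlation (ICC) of 0.06 this becomes 671.

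Under Data analysis, "A three-level logistic regression model will be used to account for variation at the NH/physician/patient level". The model drops to two levels if no physician effect is indicated. On estimation the text says: "A second-order penalized quasi-likelihood estimation procedure will be applied". Secondary outcomes are to be handled by similar multilevel models. The article does not name a test statistic, a reference distribution, degrees of freedom, or the choice between ML-type and restricted estimation.

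**The concern.** Treatment varies only between organisations, so the precision of its estimated effect depends mainly on the between-organisation variance. That variance is estimated from eleven units less two arm means. Two things can go wrong when clusters are this few. A Wald statistic referred to the normal distribution ignores the uncertainty in that variance. ML-type estimation also biases the variance downward, by roughly 9/11 here. Both make p-values too small and intervals too narrow, and so favour a finding that point-of-care testing reduces prescribing. If the analysis does allow for nine degrees of freedom, the sample size does not, and the trial has less power than stated.

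**Working it through.** **Inputs from the article.** Rates 95% and 80%; significance level 5%; power 80%; eleven organisations; ICC 0.06; 671 cases. Sidedness is not stated, but two-sided reproduces the published figure.

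**Step 1: reproduce the sample size.**
- Unpooled two-proportion formula with normal quantiles: n per arm = (1.960 + 0.842)² × (0.95×0.05 + 0.80×0.20) / 0.15² = 72.4. Rounded up, 73 per arm gives 146, the stated figure.
- The pooled formula gives 76 per arm (152) and the continuity-corrected one 88 per arm. Neither matches.
- Cases per organisation: 671/11 = 61. Design effect: 1 + 60 × 0.06 = 4.6. Then 146 × 4.6 = 671.6.

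The published figures are therefore normal-theory figures with an ordinary design effect and no allowance for few clusters.

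**Step 2: size of a 1.96 test on nine degrees of freedom (closed form).**
- Between-organisation degrees of freedom: 11 - 2 = 9.
- P(|t₉| > 1.960) = 8.2%.
- With the variance shrunk by 9/11, the effective cut-off is 1.960 × √(9/11) = 1.773, and P(|t₉| > 1.773) = 11.0%.

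**Step 3: simulation of second-order PQL under no effect.** Settings: 5 v 6 organisations, 671 cases, two-level model, logit-normal organisation effects, 1,500 runs per setting. Four settings used ICC 0.06: a rate of 87.5% with equal cluster sizes, and rates of 80%, 87.5% and 95% with a coefficient of variation of cluster size of 0.5. A fifth used ICC 0.02 at 87.5%, with coefficient of variation 0.5.

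| Estimation | Reference | Type I error, ICC 0.06 | Type I error, ICC 0.02 |
|---|---|---|---|
| ML-type PQL | normal | 9.6-11.0% | 9.9% |
| Restricted PQL | normal | 6.6-7.8% | 8.3% |
| ML-type PQL | t₉ | 5.7-6.8% | 6.7% |
| Restricted PQL | t₉ | 3.5-4.6% | 4.4% |

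Monte Carlo error is at most about 0.8 points. Runs that did not converge were dropped (about 5% at the 95% rate, almost none elsewhere).

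A separate set of simulations at ICC 0.06 (3,000 trials per setting for PQL and the permutation test, 1,500 for quadrature) gave 8-11% for ML-type PQL with a normal Wald test and 3.4-5.3% for restricted PQL with t₉. A permutation test over the C(11,5) = 462 allocations gave 4-6%. Full maximum likelihood by quadrature with a Wald test gave 10-12%, so changing the estimator alone does not solve the problem.

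**Step 4: power when the test is valid.**
- Standard error of the risk difference at 671 cases, on the plan's own basis: √[(0.0475 + 0.16)/335.5 × 4.6] = 0.0533.
- Standardised effect: 0.15/0.0533 = 2.81.
- Normal reference: Φ(2.81 - 1.96) = 80.3%, the design figure.
- t₉ reference (critical value 2.262, noncentral t with noncentrality 2.81): 70.7%.

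**The case against.** The strongest reply is that the article is a condensed account. It names the model and the estimator, but it does not say that a normal-reference Wald test or ML-type estimation will be used, nor that a correction will not be used. Those details commonly sit in a full protocol or analysis plan. This stands as far as type I error is concerned: a reader might infer that the plan's real significance level is 8-11%, but the text does not fix the analysis that would produce it. The inflation can only be stated conditionally, and its upper end applies only to ML-type estimation.

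The reply does not settle the point, because the sample size is stated, not omitted, and rests on normal quantiles. If a fuller document already specifies a valid small-sample test, the 80% power in the article is too high. If it does not, the 5% level is too low.

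Two other stronger readings should be set aside. A reader might blame second-order PQL. The simulations do not support that: its restricted version with t₉ keeps to 5% or just below, while full maximum likelihood with a Wald test is no better than ML-type PQL. A reader might also infer, from the abstract's nursing home and the body's NH organisation, that the randomised level is missing from the model. Both places count the same eleven units, the design section states the level of randomisation explicitly, and NH in the model description reads naturally as shorthand for it. This calls for clearer wording and is no evidence of a wrong model.

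**Conclusion.** The point holds in conditional form. With eleven organisations the article's 5% level and 80% power cannot both be had at 671 cases. An uncorrected normal-reference Wald test would have a type I error of about 7-8% with restricted estimation and about 10-11% with ML-type estimation. A test against t₉ has about 71% power.

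These figures assume a 5 v 6 split, which simple randomisation need not give. The type I error figures also assume a two-level model: the physician level, and its removal depending on the data, were not simulated. The power figure assumes equal clusters of 61 cases and the article's own ICC and rates.

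**What to change.** In Data analysis, keep second-order PQL but specify its restricted version. Take the primary p-value and 95% confidence interval for the treatment effect from t with organisations minus 2, that is 9, degrees of freedom. Both parts are needed, since ML-type estimation with t₉ still gives 5.7-6.8%. Add a permutation test over the possible allocations as a check. Apply the same rule to the secondary multilevel models. Name the NH organisation as the model's top level, and use that term in the abstract too; this is a clarification of wording only.

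In Sample size calculation, restate the power for 671 cases as about 71% under the t₉ test.

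The cost is a few sentences of text and minor analysis code. For a given standard error the interval widens by 2.262/1.960 = 1.15, about 15%, relative to a normal reference. The stated power falls from 80% to about 71%. No further data collection is needed for the change in analysis.
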